**Methods**

Study Design

A dual-center, single-blind (examiner), parallel design randomised control trial of 165 patients attending an outpatient cardiac rehabilitation center within two public hospitals in Sydney, Australia. See **Figure 1.** for study flow diagram. The intervention populations will receive either a tablet-delivered specifically selected series of advertisement free, web-based educational videos covering multiple CVD and oral health related topics alone or partnered with individually tailored OHI. The control population will receive usual care as detailed below. The examiner will be blinded to the group allocation.

Patient population

The study population will be patients presenting to the outpatient cardiology rehabilitation centre participating in the Cardiac Education and Assessment Program (CEAP) at Westmead and Blacktown public hospitals, Sydney Australia. CEAP provides personalised support, exercise and education to help strengthen patient’s hearts after having a cardiovascular event and helps to lower risk of a future cardiovascular event (82). These patients attend due to a range of heart conditions such as coronary heart disease, heart failure, and those waiting for, or who have had a heart transplant. Due to the variety of heart conditions and co-morbidities, patients are placed on either a 6-week or 12-week program and can attend once or twice weekly. As these patients have taken part in this program, prioritising their cardiovascular health, and showing a motivation to reduce future risk of a cardiovascular event, we predict these patients will be interested in receiving education regarding oral health impacts on CVD.

Participant eligibility

A total of 165 participants will be recruited at either Westmead or Blacktown outpatient cardiac rehabilitation clinics who are attending as part of the CEAP program. Patients 18 years or older with a recent diagnosis of CVD , recent myocardial infarction and/or recent hospitalisation resulting from CVD will be approached for screening. This will include a clinical examination consisting of periodontal screening and recording (PSR), API, and sulcus bleeding index (SBI) (83) will be completed, followed by a self-report questionnaire. Patients will be excluded if:

- they have been diagnosed with heart failure.
- have/are waiting for a heart transplant,
- are too physically or mentally unwell on the day.
- have a cognitive impairment.

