**Data collection and management**

Data will be collected at baseline, 6 weeks and at the final 12-week assessment and stored via REDCap. Baseline data will include demographic information, medical history, weight (kg), height (cm), body-mass index (BMI), oral hygiene practices, and oral hygiene knowledge associated with CVD. CEAP nurses record weight, height, and BMI when patients first attend the program, as such this data and other required medical data will be retrieved from participant clinical records. Questionnaires delivered via REDCap via iPads. Clinical parameters will be recorded at baseline, the 6-week, and the final follow-up after 12 weeks. PSR, SBI, and API will be completed using a disposable World Health Organisation (WHO) periodontal probe and mirror, with tricolour disclosing gel. For timeline and mode of collection see **Table 1**.

Each site will hold a master spreadsheet held on WSLHD servers. Identifiable data including name, address and phone numbers will be housed on secure servers within the WSLHD network. The server is managed and maintained by WSLHD Digital Health Services (DHS). Each patient will be assigned a code – the patient’s name and dental record number will be linked to the study code and stored in an encrypted and password protected folder, separate to all other data files, with access to this folder limited to the principal investigator and coordinating principal investigator. All other data files will contain only the study code. Participant consent forms will be in digital form as part of REDCap, thus stored electronically. Data sheets will contain the study code, age and sex and will be stored electronically. De-identified data will be used for any analyses and publications and all data collected during the study will be retained for a period of 5 years following the study completion. We anticipate no harm resulting from the intervention, as such we do not require a data safety monitoring board.

**Table 1.** Timing and mode of collection of study data

| Measurements and Surveys | Baseline | 6-week  Assessment | 12-week  Final Assessment |
| --- | --- | --- | --- |
| Demographic information and medical history and behaviour/risk factors | X |  |  |
| Clinical measurements PSR/API/SBI | X | X | X |
| Oral health Perceptions and knowledge | X | X | X |
| Oral hygiene habits | X | X | X |
| Motivation and confidence and to improve oral hygiene practices | X | X | X |

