**Sample size**

The required sample size for this study is calculated to be a total of 165 (1:1:1 Group A: Group B: Group C). This calculation includes provision for a 10% attrition rate, two tailed tests, type 1 error of 5%, and will have 80% power to detect any significant difference between Group A and Group C. This calculation is based from an API score reduction of 25% in the intervention arm of Ziebolz, et al 2009 study (87). However, due to our exclusion criteria of ≤59% API score, we will expect to see a 40% decrease in Group A, compared to 15% in Group C. This current study is powered to detect a difference in percentage proportion of those between Group A and Group C however, has poor power to detect a difference between Group B and Group C.

| Table 2. Adapted API/SBI measurement results (88) | | |
| --- | --- | --- |
|  | **API** | **SBI** |
| Poor oral hygiene | >35% | >25% |
| Fair oral hygiene | 35% | 15-25% |
| Good oral hygiene | <25% | <15% |

| Table 3. Adapted PSR code definitions (86,89). | |
| --- | --- |
| Code | Clinical Signs |
| 0 | Absence of clinical signs: no calculus, or BOP  Coloured band on WHO probe completely visible. |
| 1 | No calculus.  BOP  Coloured band on WHO probe completely visible. |
| 2 | Supra and/or subgingival calculus  BOP  Coloured band on WHO probe completely visible. |
| 3 | Periodontal pocket 3.5mm-5.5mm  Coloured band on WHO probe partially visible |
| 4 | Periodontal pocket >5.5mm deep  Coloured band on WHO probe no longer visible |
| X | Sextant absent of dentition |
| * | Periodontal abnormalities which include:  Furcation involvement  Mobility  Mucogingival problems for example: exudate, severe oedema  >3.5mm recession  The * is recorded next to the sextant number code. E.g. “3*” |

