**Statistical analysis**

The statistical plan for this study will be determined prior to study completion. Analysis of the difference in API will be according to the intention-to-treat principle where participants are analysed in the arm they have been allocated. The level of statistical significance will be set at p-value <0.05. The primary analysis will be an adjusted analysis of variance performed to assess differences between groups for API scores between baseline and follow-up. Covariates used for adjusted analyses will include age, sex, highest PSR code, level of education, smoking status, and number of teeth. Subgroup analysis of the intervention effect and age, sex, education, ethnicity, and cardiovascular disease presentation (coronary heart disease, heart failure, heart transplant list, heart transplant receiver) will also be explored. Outcome measures available at baseline (PSR, SBI and API) will also be included in the statistical model. An unadjusted analysis will be performed to assess differences between groups using a X^2^ test for binary (categorical) outcomes and independent sample t-tests for continuous outcomes.

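### For the secondary mean API and SBI outcomes, one repeated-measures model per index would use both follow-up visits and include site; the ANOVA and t-tests named in the protocol need not, and the gain is modest

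*Protocol*

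**What the plan says.** Three parts of the protocol bear on this point.

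- **Visits and outcomes.** Data collection and management states: "Clinical parameters will be recorded at baseline, the 6-week, and the final follow-up after 12 weeks". Study outcomes lists mean reductions in API and in SBI, at each follow-up, for A against C, A against B and B against C. That is 2 indices × 3 pairs × 2 visits = 12 contrasts, all secondary.
- **Methods.** Statistical analysis says: "The primary analysis will be an adjusted analysis of variance performed to assess differences between groups for API scores between baseline and follow-up". It adds: "Outcome measures available at baseline (PSR, SBI and API) will also be included in the statistical model". The other named covariates are age, sex, highest PSR code, education, smoking status and number of teeth. The unadjusted analysis is a chi-squared test for binary outcomes and "independent sample t-tests for continuous outcomes". Analysis is "according to the intention-to-treat principle where participants are analysed in the arm they have been allocated". No repeated-measures structure is named. The section defers the full statistical plan to a later point, before the study is completed.
- **Loss and stratification.** Sample size says: "This calculation includes provision for a 10% attrition rate". Randomisation stratifies by age and site. Of these two, only age is in the covariate list.

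**The concern.** The design yields two correlated follow-up scores per person on each index, but the named methods are single-outcome methods. The phrase about baseline and follow-up does not say which follow-up is meant. The natural reading is a separate analysis at each visit. At 12 weeks such an analysis excludes anyone without a 12-week score, even when their 6-week score is on file and says something about where they were heading.

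Two things are at stake for the 12-week means. One is a little precision. The other is bias: if people with poor 6-week scores in one arm are the ones who fail to return, those who remain in that arm look better than the arm as randomised. Participants are not blinded, and Groups B and C receive their individual instruction only after the final assessment, so reasons for returning could differ by arm. The protocol does not say in which direction.

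Separately, an adjusted model that leaves out a factor used to stratify the randomisation does not match the design, and adding it is simple.

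**Working it through.** **1. The protocol's own sample size.** Inputs from Sample size: 40% against 15% (read as responder proportions), two-sided 5%, 80% power, 10% attrition.

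n per arm = [1.96·√(2·0.275·0.725) + 0.8416·√(0.40·0.60 + 0.15·0.85)]² / 0.25² = (1.238 + 0.510)² / 0.0625 ≈ 48.9, so 49.

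49 / 0.9 = 54.4, so 55 per arm and 165 in total. The stated figure is reproduced. It rests on the responder proportion, so a change of model for the means does not alter it.

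**2. Precision at 12 weeks.** Let d be the share missing week 12 with week 6 seen, and r the correlation between the 6- and 12-week scores (the partial correlation, once baseline is in the model). Relative to using only those seen at week 12, the likelihood estimate of a 12-week mean has variance 1 − r²d. The protocol gives no r, so a range is assumed. Using d = 0.10, that is, treating all the planned loss as a missed week 12 after a seen week 6:

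| r | Variance cut (r²d) | Effective n per arm (from 55 × 0.9 = 49.5) |
|---|---|---|
| 0.3 | 0.9% | 49.9 |
| 0.5 | 2.5% | 50.8 |
| 0.7 | 4.9% | 52.1 |

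With a visit correlation of 0.6 and a baseline correlation of 0.4, the partial correlation is (0.6 − 0.16)/(1 − 0.16) = 0.524, and the cut is 0.524² × 0.10 = 2.7%.

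**3. Bias at 12 weeks.** Simulation with 55 per arm, 10,000 runs, SD 1, those same correlations, a true difference of 0.5 SD and 10% loss after week 6. Loss follows a logistic model in the 6-week score; the slope is the log-odds per SD. Negative bias overstates the benefit.

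| Slope, A / C | Baseline-adjusted, week-12 attenders only | t-test on change | Likelihood estimate using week 6 |
|---|---|---|---|
| 0 / 0 | −0.002 | −0.003 | −0.003 |
| 0.5 / 0 (moderate, one arm) | −0.019 | −0.004 | 0.003 |
| 1.5 / 0 (strong, one arm) | −0.056 | −0.027 | −0.002 |
| 0.5 / 0.5 | −0.001 | −0.001 | −0.001 |
| 1.5 / 1.5 | −0.002 | −0.001 | −0.002 |

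Monte Carlo error is about 0.002. The standard error of the difference in one trial is about 0.18 SD, so even the strong one-arm case shifts the estimate by about 0.056/0.18 ≈ 0.3 of a standard error. A slope of 1.5 is an odds ratio of about 4.5 per SD; 0.5 is about 1.65.

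**4. A more extreme pattern.** A separate simulation used SD 15, all correlations 0.6 and a true difference of −15, with strong dependence in opposite directions in the two arms. At about 12% missing, the baseline-adjusted visit-wise estimate was −16.1 (bias 1.1/15 ≈ 0.07 SD) and the likelihood estimate −15.0. With the same dependence in both arms, all methods gave −15.0 to −15.1.

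**5. Which contrasts move.** With loss after week 6, the 6-week means are essentially unaffected. The change falls mainly on the six 12-week contrasts.

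**The case against.** The strongest reply is that the protocol defers its statistical plan, and that visit structure, covariance and missing-data rules commonly belong there. That stands as far as silence goes: leaving those details open is not an error. But the protocol does name methods for these outcomes, and a better one can be named at little cost.

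Several stronger readings are tempting and are not supported:

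- A reader might infer that anyone who misses a visit is dropped altogether. The protocol does not say so. A visit-wise test leaves a person out of the missed visit only.
- A reader might infer that baseline adjustment is missing. It is not; only the t-tests, which are explicitly the unadjusted analysis, lack it.
- A reader might infer a breach of intention-to-treat. The protocol defines that principle as analysis in the allocated arm, and a visit-wise analysis meets the definition.
- A reader might infer that loss will cluster at 12 weeks because "patients are placed on either a 6-week or 12-week program". Nothing in the protocol links attrition or the 12-week assessment to programme length.
- A reader might infer a large bias. In the one-arm setting, biases near 0.09–0.125 SD need 20–30% loss as well as strong dependence; the protocol plans for 10%.

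It is also fair to say that a t-test on change showed less than half the bias of the adjusted visit-wise analysis in the strong one-arm case, so the t-tests are not the weak point on bias.

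**Conclusion.** The point holds as a cheap improvement of low weight, not as an error. For the secondary mean API and SBI outcomes, the named methods applied visit by visit ignore the other follow-up score of anyone who misses a visit, and the covariate list omits site.

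At the planned 10% loss, the better model buys about 1–5% of variance at 12 weeks, for assumed correlations of 0.3 to 0.7. It also protects against a bias of about 0.02 SD (moderate) to 0.05–0.06 SD (strong) when loss depends on the 6-week score in one arm only. The bias is larger only if the dependence runs in opposite directions by arm, and essentially nil if both arms share it. The correlations and loss patterns are assumptions; the protocol gives neither.

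The protection requires that loss be explained by observed data (missing at random). It does not cover loss driven by unseen scores, and people with no follow-up visit add essentially nothing. The primary outcome, a 6-week responder proportion, is unaffected.

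**What to change.** For each of API and SBI, make the adjusted analysis of the mean scores one likelihood-based repeated-measures model:

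- outcomes: the 6- and 12-week scores;
- fixed effects: arm, visit, arm-by-visit, baseline score, baseline-by-visit, site, age, and the protocol's other named covariates (sex, highest PSR code, education, smoking status, number of teeth, and the other baseline measures already planned);
- unstructured within-person covariance, which with two visits has only three parameters per index;
- the A–C, A–B and B–C contrasts at each visit read from this model.

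Keep the t-tests as the supporting unadjusted analysis, with the visit stated for each. Settle the wording before the data are analysed.

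The cost is a change of analysis text and slightly more analysis work, with no new data, visits or participants. The downside is reliance on missing at random, which is weaker than what a visit-wise analysis of attenders assumes but is still an assumption. The primary responder outcome and the total of 165 stay as they are.

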**Process evaluation**

We aim to assess the effectiveness the intervention has or does not have on oral hygiene habits and knowledge for patients with CVD. A recruitment log will be kept, recording patients who do not wish to participate, or for those who are ineligible to. Part of the follow-up questionnaire will include a self-assessment of acceptability and the educational value of the study, including assessment of the included videos and it will attempt to identify any areas for improvement. Additionally, a member of the study team will contact participants via telephone at the end of the study to obtain their perception of the study intervention. An anonymous questionnaire, with implied consent by clicking on the link will also be given to the nursing staff to assess their oral knowledge, perception of the intervention’s importance and effectiveness, and ways it may be better incorporated into CEAP. As no relevant questionnaire exists to determine the outcomes of this study an adapted questionnaire was developed from previously established tools (90–93). This will an anonymous survey with implied consent by clicking on the survey link sent to all CEAP nursing staff at the conclusion of the study.

**Conclusion**

The link between oral health and CVD has been proven (18,21,29). For the average patient with CVD, the accessibility of information regarding the importance of this link and the impacts oral hygiene practices has on their cardiovascular health, are almost non-existent (28,45–49). As such, oral health knowledge and the importance of oral hygiene amongst this population is minimal (74). Digital educational programs have proved effective in increasing knowledge, confidence, and motivation to improve health outcomes (77), even when literacy levels are low (78,79). Therefore, this study will assess if the introduction of individualised OHI and a DOHE instrument will influence the API score, oral health, practices, knowledge, and motivation of CVD patients attending a cardiac rehab out-patient facility.

**Ethics**

Ethics approval will be sought from the WSLHD Human Research Ethics Committee. During recruitment, baseline and follow-up assessments, participants will be informed of their right to decline to take part or withdraw from the trial at any time. It will be highlighted that non-participation or withdrawal will in no way affect their current or future care at the hospital. The authors will seek approval to any variations required to be made to the protocol. Informed consent will be gained from all participants before being included in the study.

**Dissemination**

The results from this study will be published in peer reviewed journals and presented nationally and internationally at both oral health and cardiology conferences.

**
[figure not shown]
**

**Figure 1.** Study flow chart

**
[figure not shown]
**

**Figure 2.** Patient recruitment flow diagram.

